|  |
| **6.5.3 Sample size for detection of the impact of treatment on malaria morbidity and mortality**  Based on the previous records the prevalence in the two villages is expected to be around 10%. Therefore, 216 residents from each village, out of the total of 500, will be examined to detect prevalence between 5 - 15 % at 5% level of significance with a design effect of 2.  The sample sizes were calculated using Epi-Info 2002 computer programme.  6.6. Sampling technique and randomization  Persons who were positive by PCR in the dry season will be enrolled in the study for measuring the efficacy of each combination. The list of eligible participants will be sorted according to village and age, to achieve an implicit stratification. The allocations for this ordered list will be generated using restricted randomization with a block size of 12 in Stata version 7 (Statacorp, Texas)  Simple random sampling technique will be used for the selection of the sample size needed for detecting the impact of the treatment on malaria morbidity.  6.7. Data Collection methods, instruments used, measurements  6.7.1.Describe the instruments used for data collection (questionnaire,observation recording form, etc..), studied variables included in these instruments, and methods used to test for the validity and reliability of the instrument.   - Clinical data will be collected by a medical doctor using a questionnaire. - Thin and thick blood films will be collected on slides by finger brick - A parallel drop of blood will be collected on filter paper from the same finger brick for screening by conventional nested PCR technique. - Microvet tubes will be used to collect 150 ul of blood by finger brick from PCR positive individuals only. Samples will be used for detection of subpatent gametocytes by RT-PCR.     6.7.2.Techniques used should be briefly described and referenced  Thin and thick blood films will be stained and used for species identification and parasite density estimation13.  **Detection of low level *P. falciparum* infection during the dry season**  *P. falciparum* DNA will be extracted from filter papers of microscopically negative blood samples14.  Nested PCR will then be used to detect low level *P. falciparum* infections that prevail during the dry season15. Principal genes to be detected are *Pfs*25 and *Pfg*377, which encode gametocyte specific proteins. Results will then be visualized using gel electrophoresis. Detection of gametocytes using RT-PCR RT-PCR method will be used for detection of sub-patent gametocytemia during the dry season16, 17. Briefly, blood samples collected for RNA isolation and RT-PCR of *Pfs25* and *Pfg377* will first be left at room temperature for 30 minutes, to allow exflagellation and microgamete formation. The plasma and the buffy coat will be removed and the red blood cells stored at -70°C. Total RNA will be isolated using RNA isolation kits. RT-PCR of RNA will then be carried out.   - - 1. **Study definitions (eg case definition) should be mentioned.**   Clinical malaria includes those with microscopically diagnosed *P. falciparum* and clinical symptoms.  Sub-patent parasitaemia includes those detected positive by PCR  Gametocyte reservoirs include those detected positive by the RT-PCR.  **6.8.Data Management and Statistical Analysis**  (Describe the overall plan and tests used for data analysis and statistical package used)  The efficiency of the two treatment regimens will be assessed by comparing the proportions detected positive for asymptomatic infections before and after treatment. Comparison will be done using chi-square test and the significance of the results will be measured by the *P-value*.  Malaria prevalence and percent of mortality will be determined from data collected during the transmission season survey. They will be used for evaluation of the intervention by comparing them between the two villages and with data of the previous transmission season for every village. Comparison will also be done by chi-square test.  The data will be analyzed using SPSS (Statistical Package for Social Science) version 10. |

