
| 1. Implications of study results on disease control    1. Expected results and potential contribution of the project to the relevant control programme   It is expected that by the end of this study the suitable and highly effective combination therapy of antimalarial drugs will be identified. The strategy of treating sub-patent parasiaetimia and gametocyte carriage during the dry season is expected to have great impact in malaria morbidity and mortality in the intervention villages during the transmission season. If the expected results are achieved, this strategy of treatment during the dry season with the identified drugs will be recommended to be incorporated into the national malaria control programme of the Ministry of Health for controlling malaria epidemics in areas of marked seasonal transmission.   - 1. Mechanisms to ensure implementation of research results in the health policy of the concerned control programme of the Ministry of Health - A community physician from Malaria, Schistosomiasis and Leishmaniasis Control programme, Federal Ministry of Health(Deputy Director),is co-investigator in the project. He will be in close contact with the progress of the project and its activities and will be aware by the results. - Copies of the progress reports and the final report will be sent to the Control Prgramme. - Formal meeting can be arranged with the staff of the control programme to discuss the findings of the project and the possibility of implementing them. |
| --- |
| 1. Areas of Integration of Research Activities (if applicable)   The project integrates very well with the activities of a national malaria project (SUD 06/21) receiving TC support from the International Atomic Energy Agency (IAEA). This project will benefit from its field and laboratory facilities. [name] [name], U. of Edinburgh, will supervise the RT-PCR part and we will use the field station in Gadarief rent to his MRC malaria project in the area. [name], Medical statistician in the MRC laboratories in the Gambia, greatly helped in the design and will help in statistical analysis and publication of the work. |

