| 1. Ethical Considerations    1. Informed consent form (If needed, please attach extra documents)  - Preliminary meetings will be held with the community leaders to inform them about the project and its objectives and to ask for their permission and collaborating in passing the message to the community. - A signed informed consent form will be collected from householders stating their agreement to participate. Even within each household, blood samples will be collected from those who are willing to participate. - Blood samples will be collected by a qualified laboratory technician with experience of more than 15 years in this field. This will be done under supervision of a medical doctor. - Clinical investigations for all patients, including those with common diseases, during every survey will be carried out by a medical doctor. He will also be responsible for prescription of drugs and very close clinical monitoring specially for those who will be given antimalarial drugs. - The principal investigator is committed to provide drugs for malaria and for other common diseases to those who will be detected sick during the surveys.      - 1. Institutional ethical clearance   Do you have an ethical review board in your institution: Yes [ ] No [ X ]  If no, then the ethical clearance of the Ministry of Health could be accepted.  (To be amended in case of initial acceptance by the selection committtee) |
| 1. Other funding agency   Is your study funded by another funding agency: Yes [ x ] No [ X ]  (specify the agency and available funds)  TC grant from the IAEA. |

| **12. Timeframe of research activities** (please indicate the activities to be conducted and check the corresponding month) | | | | | | | | | | | | |
| --- | --- | --- | --- | --- | --- | --- | --- | --- | --- | --- | --- | --- |
| Activity | 1st QUARTER | | | 2nd QUARTER | | | 3rd QUARTER | | | 4th QUARTER | | |
|  | M1 | M2 | M3 | M4 | M5 | M6 | M7 | M8 | M9 | M10 | M11 | M12 |
| ***Transmission season of 2003 survey*** |  |  |  |  |  |  |  |  |  | **X** | **X** |  |
| ***Dry season field survey*** |  |  | **X** |  |  |  |  |  |  |  |  |  |
| ***Nested PCRs*** |  |  |  | *X* | *X* |  |  |  |  |  |  |  |
| ***Samples for RT-PCR*** |  |  |  |  | ***X*** |  |  |  |  |  |  |  |
| ***RT-PCRs*** |  |  |  |  | X | X |  |  |  |  |  |  |
| ***Submission of the Progress Report*** |  |  |  |  |  | X |  |  |  |  |  |  |
| ***Pre-transmission field survey*** |  |  |  |  |  |  | *X* |  |  |  |  |  |

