| ***Treatment &***  ***Drug testing*** |  |  |  |  |  |  | X | X | X |  |  |  |
| ***Transmission season survey*** |  |  |  |  |  |  |  |  |  |  | ***X*** |  |
| ***Submission of the Final Report*** |  |  |  |  |  |  |  |  |  |  |  | X |

| **13. Outline of budget**    Total amount of budget: US$* 10 000 | |
| --- | --- |
| **Budget breakdown:** | **Budget (US$)** |
| Personnel**  _ Medical doctor  _ Two Technicians  _ Research assistant  _ Driver  The team will be involved in four field surveys, 5 days each | **2 000** |
| Supplies and Equipment  _ Reagents  _ Disposable  _ Chemicals  _ Consumables | **2 000** |
| Local Travel  To cover expenses of travel to the study area for four surveys (5 days each) and working there between the village and the field station in Gadarief town. | **3 500** |
| Patient Costs  Mainly for drugs | **1 500** |
| Training |  |
| Others (please, specify and justify briefly)  _  _  _  _ |  |
| **Total** | **9 000** |

*Not exceeding 10,000 US$

** Only a limited proportion of the funds should be allocated to the personnel

| **14. Other information (if needed, please add any other information)** |
| --- |
| **15. Annexes (Data collection instruments, elaboration on methods and procedures to be used, etc..) (Please attach the related documents)** |

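### The between-village test cannot measure the intervention, because both villages receive both regimens, and the comparison with the previous season has no concurrent control

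*Protocol*

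**What the plan says.** Four parts of the protocol bear on this.

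- **Objective (5.2).** Evaluating the effect of the strategy on transmission-season morbidity and mortality is one of four specific objectives. Section 5.3 lists no secondary ones.
- **Allocation (6.6).** The people randomised are individuals: "Persons who were positive by PCR in the dry season will be enrolled in the study for measuring the efficacy of each combination". Village enters only through the ordering: "The list of eligible participants will be sorted according to village and age, to achieve an implicit stratification". Then: "The allocations for this ordered list will be generated using restricted randomization with a block size of 12". Section 6.3 gives two active regimens, with and without primaquine, and no untreated group.
- **Impact analysis (6.8).** On prevalence and mortality in the transmission season: "They will be used for evaluation of the intervention by comparing them between the two villages and with data of the previous transmission season". The sentence goes on to say that the comparison with the earlier season is made for each village separately. The method follows: "Comparison will also be done by chi-square test".
- **Use of the result (Implications of study results on disease control).** The strategy "is expected to have great impact in malaria morbidity and mortality in the intervention villages during the transmission season". If the expected results are achieved, it will be recommended for the national control programme.

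**The concern.** Section 6.8 treats the villages as if they were the units that received different interventions. Under 6.6 they are strata, each with the same planned mix of the two regimens. A significant difference between the villages would then be a difference between two places, yet 6.8 would report it as an evaluation of the intervention.

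The second comparison, each village against its own previous season, does contrast a time before treatment with a time after it. But everything else that changed between the two seasons is included in the difference, and no village or group shows what would have happened without treatment.

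A stated objective thus has a stated analysis that cannot answer it, and the result feeds a conditional recommendation for national policy. No later analysis plan can repair this, because the missing control is a feature of the design.

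**Working it through.** **Inputs.** Prevalence about 10%, range 5% to 15%, 216 residents examined per village, village size 500, design effect 2 (6.5.3). Dry-season carriage about 15% (6.5.1). Block size 12 (6.6). Allocation 1:1, so six and six per block, is inferred from the equal arms in 6.5.2.

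**1. What 216 was calculated for.** Precision of one proportion, with a finite population correction:

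- n0 = 1.96² × 0.10 × 0.90 / 0.05² = 138.3
- n = 138.3 / (1 + 138.3/500) = 108.3, rounded to 108
- 108 × 2 = 216

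The protocol's figure is reproduced, reading 500 as the size of each village. It is the number needed to estimate one prevalence to within 5 points, not a power calculation for either comparison in 6.8.

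**2. How far the regimen mix can differ between villages.** Take 0.15 × 500 = 75 carriers per village.

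- The first village on the list fills 6 whole blocks (72 people, 36 on primaquine) and takes 3 people from the seventh block. Its primaquine count is 36 to 39.
- The second village takes the other 9 people of that block, then 5 whole blocks (60 people, 30 on primaquine), then 6 people of a last block. If the first village has 36, the second has 6 + 30 + (0 to 6) = 36 to 42. If the first has 39, the second has 3 + 30 + (0 to 6) = 33 to 39.
- The largest gap is 6 people: 6/75 = 8 points of carriers, or 6/500 = 1.2% of residents. The expected gap is 0.

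With 55 carriers per village instead (110 enrolled, split evenly), the same count gives a largest gap of 6/55 = 10.9 points of carriers, again 1.2% of residents.

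**3. What the year-on-year test would do with natural change.** Assume 216 examined in each season and no drug effect at all. With p̄ the mean of the two prevalences, the chance of a significant chi-square is

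Φ{ [|p1 − p2| − 1.96 √(2p̄(1 − p̄)/n)] / √[(p1(1 − p1) + p2(1 − p2))/n] }

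For 15% falling to 5%, n = 216: (0.10 − 1.96 × 0.02887) / 0.02846 = 1.525, which gives 93.6%. If the design effect of 2 applies, the effective n is 216/2 = 108:

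| Assumed natural change | n = 216 | effective n = 108 |
|---|---|---|
| 15% to 5% | 93.6% | 69.0% |
| 15% to 10% | 34.8% | 19.7% |
| 10% to 5% | 50.5% | 28.5% |

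The changes are illustrations taken from the protocol's own 5% to 15% range. The documents do not say how much prevalence varies from year to year.

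**4. Whether the two comparisons can be combined.** Subtracting one village's change from the other's does not isolate treatment either, since both villages receive the same planned mix in the same season.

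**The case against.** The strongest defence is in section 6.1: the villages are matched for malaria burden, environment and control measures, conditions are relatively stable, and no change in control measures is expected. This is a real safeguard against one rival explanation of a before-after change, a new control activity. It does not remove natural variation in transmission between seasons. For the between-village test, matching only brings the expected difference closer to nil.

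It is also fair to say that 6.8 already plans the seasonal comparison by village, that the policy statement is conditional and rests partly on identifying the better regimen, and that the day-3 comparison between randomised individuals is unaffected by this problem. All of that stands. None of it supplies a control for the impact objective.

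Three stronger readings are tempting, and the documents do not support them.

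- **That the surveys fall in different months.** Section 12 marks the "Transmission season of 2003 survey" in M10 and M11 and the later "Transmission season survey" in M11, so the windows overlap. The budget allows 5 days per survey, so the two marks may be a scheduling window or one visit that straddles two months. A mismatch is possible but not shown.
- **That the village comparison contains no treatment effect whatever the efficacy.** This holds in expectation, and with similar carriage and coverage in the two villages. If those differ, the amount of treatment differs and some effect enters, mixed with the effect of place.
- **That the day-3 result could carry the policy recommendation instead.** It compares two active regimens. It can inform the choice between them, but cannot show that dry-season treatment reduces morbidity or mortality.

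**Conclusion.** The point holds. The between-village chi-square in 6.8 cannot estimate a regimen effect or a treated-versus-untreated effect. Under the allocation in 6.6 the planned difference in regimen mix is nil, and the worst case from split blocks is 1.2% of residents. This assumes 1:1 allocation, similar carriage and coverage, and 55 to 75 carriers per village.

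The comparison with the previous season can describe a change but cannot attribute it. The size of the possible error cannot be fixed from the documents. Within the protocol's own prevalence range, a purely natural change would give a significant test with probability between about 20% and 94%, depending on the change assumed and on whether the design effect applies.

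This should be corrected before the analysis is run, because the analysis as written would present a place or year difference as the impact of the intervention on a listed objective.

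**What to change.** - **6.8:** delete the between-village test as an evaluation of the intervention. Report the 2003 to 2004 change in prevalence for each village, as already planned, and for both pooled, with a 95% confidence interval. Label it descriptive and uncontrolled, and state that the interval covers sampling error only, not variation between years.
- **5.2, 6.4, the heading of 6.5.3, and the section on implications for disease control:** reword to match, so that the study does not claim to demonstrate an impact on morbidity or mortality. State that the randomised day-3 comparison informs only the choice between the two regimens.
- **Survey timing:** do not restrict the 2003 data to M11. If that 5-day survey fell in M10, nothing would remain. At most, schedule the 2004 survey for the same calendar dates as the 2003 survey.

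The cost is wording and a more modest claim on impact. No data are lost, and sample size and randomisation are unchanged. Making each village an arm would not rescue the claim: with one village per regimen there is no estimate of variation between villages. A real impact estimate would need several villages per condition, including untreated ones, which is a different study.

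### Section 6.8 judges the strategy's impact by a between-village test that cannot measure it and by one year-on-year question tested twice on half the data; one village-stratified before-after comparison should be the main analysis.

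*Protocol*

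**What the plan says.** Protocol section 6.8 states: "Malaria prevalence and percent of mortality will be determined from data collected during the transmission season survey". The intervention is then to be evaluated by "comparing them between the two villages and with data of the previous transmission season for every village", and "Comparison will also be done by chi-square test". For prevalence this gives three tests: village against village after the intervention, and 2003 against the post-intervention season in each village. Mortality is handled in the same way.

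Section 6.5.3 sets the survey size. It says that "the prevalence in the two villages is expected to be around 10" percent and that "216 residents from each village, out of the total of 500, will be examined to detect prevalence between 5 - 15" percent, "at 5% level of significance with a design effect of 2". Section 6.6 specifies simple random sampling for this survey. It also orders the list of treatment participants by village and age before individual allocation in blocks of 12, so both regimens are used in both villages.

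The section on implications for disease control says: "If the expected results are achieved, this strategy of treatment during the dry season with the identified drugs will be recommended". It does not say which comparison would show this.

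**The concern.** The evaluation of impact is one of the protocol's specific objectives, and a recommendation to the national control programme is to follow from it. The comparisons chosen do not fit the design. Drug allocation is by individual within a list sorted by village, and carriers in both villages are treated. A difference between the villages after the intervention is therefore no measure of what the strategy did. The year-on-year change does bear on the question, but it is the same question in both villages, which section 6.1 describes as matched for malaria burden, environment and control measures. Testing it once per village gives two opportunities for a chance finding, and each test uses half of the available data. The plan also gives no reading for a significant fall in one village and not in the other.

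**Working it through.** **Inputs from the protocol.** Prevalence 10%, range 5% to 15%, 216 people per village out of 500, 5% level, design effect 2 (all 6.5.3); the comparisons and the chi-square test (6.8); simple random sampling (6.6).

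**Assumptions.** 216 per village in 2003 as well (not stated), and independent observations, which ignores residents sampled in both seasons.

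**1. The plan's own figure.** For one proportion estimated to within 5 points:
- n0 = 1.96² × 0.10 × 0.90 / 0.05² = 138.3
- finite population correction: 138.3 / (1 + 138.3/500) = 108.3
- times design effect 2: 216.7, or 2 × 108 = 216.

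The 216 is reproduced. It is the size for estimating prevalence in one village, not for any comparison in 6.8.

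**2. False positives when nothing changes (10% throughout).**
- Significant fall in at least one village: 1 − (1 − 0.025)² = 0.049. One combined test: 0.025. Simulation of 1,000,000 trials also gives 4.9% for the former.
- Either year-on-year test significant in either direction: 1 − 0.95² = 0.0975; simulated 9.7%.
- Any of the three tests in either direction: 1 − 0.95³ = 0.143 if they were independent. The between-village test shares data with each year-on-year test (correlation about 0.5 in size), and simulation gives 12.8%.

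**3. Power for a fall from 10% to 5% in both villages, two-sided 0.05.** With mean prevalence 0.075,

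power = Φ{[0.05 − 1.96 √(2 × 0.075 × 0.925 / n)] / √[(0.09 + 0.0475) / n]}

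- n = 216 (one village): (0.05 − 1.96 × 0.02535) / 0.02523 = 0.01, power 0.505
- n = 432 (both villages): (0.05 − 1.96 × 0.01792) / 0.01784 = 0.83, power 0.798; simulated 81%.

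**4. Agreement between the villages in that case.** With p = 0.505:
- exactly one significant: 2p(1 − p) = 0.50
- both significant: p² = 0.26
- neither: (1 − p)² = 0.245.

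The between-village test is significant in about 5% of trials, as it would be with no effect at all, because both villages fall equally.

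**5. Other effect sizes.**

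| True fall in both villages | Power, one village (216 vs 216) | Power, combined (432 vs 432) | Exactly one village significant |
|---|---|---|---|
| 10% to 5% | 51% | 80% | 50% |
| 10% to 6% | 33% | 58% | 44% |
| 10% to 7% | 20% | 35% | 32% |

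For 10% to 7%, the commonest result is that neither village is significant: (1 − 0.20)² = 64%.

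**The case against.** **The any-of-three error rate.** A reader might infer that the false-positive rate is 12.8%. That needs a rule that any significant result counts as impact, including a rise or a difference between two treated villages. The protocol states no such rule. Counting falls only, the figures are 4.9% and 2.5%. Requiring a fall in both villages is also an open reading, and it would make the error smaller than nominal, not larger. This objection stands, and the smaller figures are the ones to use.

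**Disagreement as the expected pattern.** It is tempting to say that disagreement between the villages is always the likeliest result. That is so only when 2p(1 − p) exceeds both p² and (1 − p)², that is, for single-village power between 1/3 and 2/3. It holds at 10% to 5% but not at 10% to 7%.

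**The design effect.** If observations truly carried a design effect of 2 and the chi-square ignored it, the any-of-three figure would be about 38%. But 6.6 specifies simple random sampling, which does not itself create such an effect. The tension between 6.5.3 and 6.6 is a separate matter and does not support this point.

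**Either-village power.** With a fall from 10% to 5%, at least one village is significant in about 76% of trials (1 − 0.245), not far below the combined test. That is true, but it comes at twice the false-positive rate, and in most of those trials the villages disagree.

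**Season-to-season change.** The strongest objection is that pooling does not make a before-after comparison sound. Both villages share the same two seasons and there is no untreated control. If seasons vary with a standard deviation of 0.2 on the logit scale (an assumption, for illustration) and treatment does nothing, the combined two-sided test rejects in about 22% of trials. Testing each village and accepting either gives about 25%. So the combined test does not hold its error at 0.05 against seasonal change, although it does no worse than either-village testing.

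**Left to an analysis plan.** An order of tests is commonly set in an analysis plan. Here, however, the protocol itself fixes these comparisons as the evaluation, and one of them does not address the question. The point concerns what is stated.

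**Conclusion.** The point holds, within limits. The between-village chi-square does not estimate the effect of the strategy, and splitting the year-on-year change by village lowers the power of each test from about 80% to about 50% for a fall from 10% to 5%. It also doubles the chance of a false claim of a fall, from 2.5% to 4.9%, if a fall in either village is accepted. These figures rest on 216 people per village in 2003, which the protocol does not state, and on independent observations.

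The documents do not support saying that the plan has a 13% or 38% error rate, that disagreement between the villages is the expected outcome at every effect size, or that one combined test would keep the error at 5% whatever the seasons do. The combined comparison is the better use of the same data. It remains a before-after association.

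**What to change.** In 6.8, make the main impact analysis one comparison of malaria prevalence between the 2003 and post-intervention seasons, both villages together and stratified by village (Mantel-Haenszel, or logistic regression with season and village), with a 95% confidence interval. Report the village-specific changes and the between-village comparison descriptively. State the 2003 sample size. Tie the condition for the recommendation in the implications section to this analysis. Say in both places that it cannot separate the strategy from season-to-season change and so cannot alone establish impact.

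The cost is wording in two sections and one standard analysis, with no new data. The downside is that a fall in one village can no longer be claimed as success on its own.
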